### 2.5 Data Analysis

Data analysis will be performed using SPSS 26.0 software (IBM, New York, USA). P<0.05 was regarded as statistically significant unless otherwise specified. Descriptive statistics included the mean ± standard deviation for normal distributions, median and interquartile range for otherwise, and frequency and percentage for categorical variables. Intention-to-treat analysis (ITT) will be used and multiple imputations will be handled to manage missing data. Baseline descriptive data between the control group and the intervention groups will be compared using the chi-square test for categorical variables, and ANOVA for continuous variables. The primary outcome of HbA1c will be expressed as the mean HbA1c values with standard deviations, and ANOVA will be used to compare HbA1c between groups. According to the data distribution characteristics, ANOVA or Wilcoxon rank sum test will be used to compare the changes in secondary variables within and between groups. If the difference is significant, pairwise comparisons will be performed with adjustment for multiple comparisons, and ANCOVA will be used with confounding factors such as sex and age as covariates. Spearman’s correlation analysis and partial Spearman’s correlation analysis adjusted for sex and age will be used to evaluate the relationship between changes in intestinal microbial abundance and other markers.

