#### 2.1.1 Participants

The target population of the trial will be LADA patients between the ages of 30 and 70. Participants will be recruited at a large tertiary first-class hospital in Hunan, China. The following inclusion criteria will be used in the recruitment:

Participants of both sexes aged 30 to 70 with a BMI between 18.5 and 37.5 kg/m^2^; with diabetes diagnosed according to the diagnostic criteria of the World Health Organization (WHO) in 1999; positive glutamic acid decarboxylase antibody (GADA) and HbA1c level ≥ 7.0% and ≤ 10.0%; being insulin-independent for more than 6 months after diagnosis; diabetes duration less than 5 years; fasting serum C-peptide (FCP) level ≥0.15 nmol/L, or 2-hour postprandial C-peptide (2hCP) level ≥0.3 nmol/L; and providing written informed consent will be included.

Participants will be excluded from the trial if they (1) have severe liver dysfunction (ALT and AST levels greater than three times the upper limit of detection); (2) have an eGFR < 50 ml/min/1.73 m^2^; (3) have evidence of acute or chronic infection affecting glycemic control within 4 weeks prior to the first visit; (4) have a history of any malignancy; (5) are pregnant/breastfeeding women; (6) have secondary diabetes; (7) have acute complications (ketoacidosis, lactic acidosis or hyperosmolar coma); (8) have severe organic heart disease, including but not limited to congenital heart disease, rheumatic heart disease, hypertrophic or dilated cardiomyopathy, etc., New York Heart Association (NYHA) heart function classification ≥Grade III; (9) have used corticosteroids or immunosuppressants for over 3 months, or other medications that can cause gastrointestinal reactions 2 months before recruitment and throughout the whole study period; (10) have a history of hemolytic anemia or glucose-6-phosphate dehydrogenase deficiency; and (11) are allergic to berberine hydrochloride or any components in the combinations.

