#### 2.1.2 Sample Size Determination

Sample size was determined using published data from a 12-week clinical trial with BBR and probiotics, in which the drugs decreased HbA1c by 0.44% in people with T2D (Zhang, Gu et al., 2020), assuming a common within-group standard deviation (SD) of 0.80% and a two-sided α level of 0.05. With these assumptions, a sample size of 53 evaluable subjects per arm provided 80% power to detect a difference from placebo. Considering the reasonable attrition during the study, we planned to enroll 60 patients per group (i.e., a total of 240 patients).

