### 2.4 Outcome Assessment

#### 2.4.1 Primary and Secondary Outcomes

The primary outcome measure is the change in mean HbA1c level, measured at baseline and 3 months post-intervention, which reflects the blood glucose management status of the participants.

The secondary outcome measures include: (1) the frequency of hypoglycemic events and drug-related side effects; (2) the change in C-peptide for assessing β-cell function and the incidence of acute and chronic diabetes complications; (3) daily insulin dose and medical service utilization, such as diabetes-related hospital admissions and emergency visit rate; (4) the alteration of gut microbiota assessed by multiomics measurements and the differences in intestinal permeability; and (5) the quality of life assessed by the Audit of Diabetes Dependent Quality of Life (ADDQoL-19) containing physical functioning, symptoms, psychological well-being, social well-being, role activities and personal constructs with its Chinese version CN-ADDQoL also having the individualized properties, satisfactory reliability and validity (Cronbach’s alpha=0.941) (26).

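### The primary HbA1c comparison is an ANOVA without baseline HbA1c, and the text leaves unclear whether values or changes are tested; a baseline-adjusted model would gain precision at no cost

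*Protocol article*

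**What the plan says.** Section 2.4.1 (Primary and Secondary Outcomes) defines the endpoint: "The primary outcome measure is the change in mean HbA1c level, measured at baseline and 3 months post-intervention".

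Section 2.5 (Data Analysis) describes a different quantity: "The primary outcome of HbA1c will be expressed as the mean HbA1c values with standard deviations". It then names the test: "ANOVA will be used to compare HbA1c between groups". The next sentence does speak of changes, but only for other endpoints: ANOVA or a rank test "will be used to compare the changes in secondary variables within and between groups".

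What follows is conditional: "If the difference is significant, pairwise comparisons will be performed with adjustment for multiple comparisons". The same sentence adds that "ANCOVA will be used with confounding factors such as sex and age as covariates". Baseline HbA1c is not named as a covariate anywhere.

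Section 2.1.2 (Sample Size Determination) takes its effect from an earlier trial "in which the drugs decreased HbA1c by 0.44% in people with T2D". It assumes a common within-group SD of 0.80% and arrives at 53 evaluable subjects per arm for 80% power against placebo. It does not say whether 0.80 is the SD of change or of the 3-month value.

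HbA1c is measured before treatment (section 2.1, section 2.4.3 and Table 1). Randomization is stratified by BMI and chronic complications, not by HbA1c.

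**The concern.** There are two linked problems.

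First, the endpoint and its test do not match as written. One section defines a change; the other summarises and compares values. Two analysts following the article could analyse different quantities.

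Second, on either reading the stated test ignores the baseline measurement of the same variable. That measurement normally explains part of the variation in the month-3 value. Leaving it out makes the standard error larger than it need be. The ANCOVA in section 2.5 does not repair this: it comes after a significant result, so it would not be run after a null ANOVA, and its stated examples are sex and age.

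At stake are the precision of the trial's primary comparison and whether the 80% power in section 2.1.2 applies to the quantity that will be analysed.

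**Working it through.** **Inputs from the article.** Difference 0.44, SD 0.80, two-sided alpha 0.05, 53 evaluable per arm (section 2.1.2).

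**Assumptions not in the article.** The correlation r between baseline and month-3 HbA1c runs from 0.3 to 0.8, and the variance is the same at both times.

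**Step 1: reproduce the plan's figure.** Normal approximation: n = 2 × [0.80 × (1.960 + 0.842) / 0.44]² = 51.9, so 52 per arm. With the two-sample noncentral t, power is 79.3% at 52 and 80.1% at 53. The stated 53 is therefore right for one pairwise contrast, provided 0.80 is the SD of the quantity analysed.

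**Step 2: formulas.**
- SD of change = SD of values × √(2(1 − r))
- ANCOVA residual SD = SD of values × √(1 − r²)
- If 0.80 is the SD of change, SD of values = 0.80 / √(2(1 − r)), and the ANCOVA residual SD = 0.80 × √((1 + r)/2)

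Example at r = 0.6. If 0.80 is the SD of values, the ANCOVA residual SD is 0.80 × √0.64 = 0.640. If 0.80 is the SD of change, the SD of values is 0.80 / √0.80 = 0.894 and the ANCOVA residual SD is 0.80 × √0.80 = 0.716.

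**Step 3: power at 53 per arm.** One pairwise contrast, noncentral t with 104 degrees of freedom; the single degree of freedom spent on the covariate is ignored.

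*If 0.80 is the SD of month-3 values:*

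| r | ANOVA of values | ANCOVA residual SD | ANCOVA power |
|---|---|---|---|
| 0.3 | 80% | 0.763 | 84% |
| 0.4 | 80% | 0.733 | 86% |
| 0.5 | 80% | 0.693 | 90% |
| 0.6 | 80% | 0.640 | 94% |
| 0.7 | 80% | 0.571 | 98% |
| 0.8 | 80% | 0.480 | 99.7% |

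*If 0.80 is the SD of change:*

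| r | SD of values | ANOVA of values | ANCOVA residual SD | ANCOVA power |
|---|---|---|---|---|
| 0.3 | 0.676 | 91% | 0.645 | 94% |
| 0.4 | 0.730 | 87% | 0.669 | 92% |
| 0.5 | 0.800 | 80% | 0.693 | 90% |
| 0.6 | 0.894 | 71% | 0.716 | 88% |
| 0.7 | 1.033 | 58% | 0.738 | 86% |
| 0.8 | 1.265 | 43% | 0.759 | 84% |

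**Step 4: what the tables show.** The SDs of values and of change coincide only at r = 0.5. Below that, analysing values is more precise than analysing change; above it, less precise. ANCOVA has the smallest SD at every r shown, and its power stays at about 84% or more under either reading of 0.80.

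**The case against.** **The mismatch may be loose wording.** Both the abstract and section 2.4.1 define the outcome as change, and section 2.1.2 sizes the trial on a decrease. Comparing HbA1c may be shorthand for comparing that outcome. If outcome, SD and test all refer to change, the plan is coherent at 80% power. This reading is possible, and it would remove the conflict between values and change. It does not supply the baseline adjustment: with 0.80 as the SD of change, ANCOVA still has 84% to 94%.

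**The covariate list is open-ended, and a full list may sit in an analysis plan that is not shown.** Sex and age are given only as examples, so baseline HbA1c is not excluded. That stands. But the ANCOVA is tied to a prior significant result, so even a longer list would not change the stated primary test. The point disputes a method the article does state, not a detail it omits.

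**Stronger readings that the article does not support.**
- A reader might infer that chance imbalance in baseline HbA1c biases the result. Under randomization it does not: the unadjusted standard error already allows for such imbalance, and type I error is controlled.
- A reader might infer that the trial is badly underpowered, for instance by taking 58% from the second table. That figure needs 0.80 to be the SD of change, values to be analysed, and r = 0.7. Under the same first two conditions, power is 91% at r = 0.3. No correlation is given in the article, so only the range can be reported.
- A reader might derive the spread of HbA1c from the entry criterion ("HbA1c level ≥ 7.0% and ≤ 10.0" percent). That range applies at screening, before the one-month washout on insulin, and the article says nothing about the distribution within it. Insulin adjustment afterwards may narrow the spread and weaken the correlation.
- A reader might take these powers as those of the four-arm ANOVA. They are for one pairwise contrast; omnibus power depends on all four means.

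**Conclusion.** The point holds as a loss of precision and an unclear definition of what is tested, and it should be fixed. It is not a validity defect, and the sample-size arithmetic is correct.

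The size depends on two unknowns: which SD 0.80 is, and r. If 0.80 describes values, the plan has its 80% and ANCOVA would add roughly 4 to 20 percentage points (84 − 80 at r = 0.3; 99.7 − 80 at r = 0.8). If 0.80 describes change but values are analysed, power can be above or below the plan, from 91% down to 43%, while ANCOVA stays between 94% and 84%. All of this assumes equal variances at the two times. The recommendation does not depend on which case is true, because ANCOVA is at least as precise throughout the range.

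**What to change.** - In section 2.5, make the primary analysis a linear model (ANCOVA) of month-3 HbA1c, or of change, on treatment arm with M0 HbA1c as covariate. Values and change give the same treatment estimate once baseline is in the model.
- Fit it whatever any prior ANOVA shows, and report adjusted mean differences with 95% confidence intervals for the contrasts.
- Align sections 2.4.1 and 2.5 so that both name the same quantity.
- In section 2.1.2, state whether 0.80 is the SD of change or of month-3 values.

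The cost is a change of wording before unblinding. Baseline HbA1c is already collected, so no patient, visit or measurement is added.

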## 2 Methods

### 2.1 Trial Design

This is a prospective, randomized, double-blinded, placebo-controlled trial with a 1-month washout period, a 1-week run-in period, a 3-month treatment period, and a 9-month follow-up period. The participants will be arranged to enter a 1-month washout period after obtaining their informed consent during which basic treatment medications are adjusted, and then they will be allocated to enter a 1-week run-in period for lifestyle education and collection of baseline data and samples. After the run-in period, they will be randomized 1:1:1:1 to one of four groups: BBR-alone, inulin plus BBR, inulin-alone, or placebo. This study will use a stratified random method to balance the following factors: BMI ≥25 kg/m^2^ and <25 kg/m^2^, with or without chronic complications of diabetes. Measurements will be implemented at baseline prior to the intervention and at 3 months, 6 months, 9 months and 12 months from baseline. The research flowchart is shown in **Figure 1**.

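### For non-normal secondary outcomes, the two-sample Wilcoxon rank sum test is named for paired within-arm change and as the overall test across four arms; it fits neither use

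*Protocol article*

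**What the plan says.** Section 2.5 (Data Analysis) gives one rule for testing secondary outcomes, with the choice depending on the distribution of the data: "ANOVA or Wilcoxon rank sum test will be used to compare the changes in secondary variables within and between groups". The next step is conditional: "If the difference is significant, pairwise comparisons will be performed with adjustment for multiple comparisons". So the first test is an overall test, and the pairwise tests follow only if it is significant.

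Section 2.1 (Trial Design) fixes the structure to which this rule applies. There are four arms: "they will be randomized 1:1:1:1 to one of four groups: BBR-alone, inulin plus BBR, inulin-alone, or placebo". The same patients are measured repeatedly: "Measurements will be implemented at baseline prior to the intervention and at 3 months, 6 months, 9 months and 12 months from baseline". Table 1 shows that not every outcome is taken at every visit. Quality of life, gut microbiota and intestinal permeability are marked at M0, M3 and M12 only.

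Section 2.5 names no signed-rank, paired t, Friedman, repeated-measures or Kruskal-Wallis procedure.

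**The concern.** The sentence gives the rank sum test two tasks that it cannot do.

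- **Within an arm**, a change compares a patient's follow-up value with the same patient's baseline. The rank sum test treats the two sets of values as coming from unrelated patients. Ordinary one-way ANOVA over visits would make the same mistake, and the text does not say that a repeated-measures form is meant.
- **Between arms**, the gate before pairwise testing has to compare four groups at once. A two-sample test has no four-group version under that name, so for non-normal variables the overall step is undefined.

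At stake is the reading of skewed continuous secondary outcomes, for example C-peptide or insulin dose if they prove non-normal. Real within-arm changes could be missed, and the analyst must improvise the overall between-arm test.

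**Working it through.** **Inputs from the protocol article.** Four arms, 1:1:1:1 (section 2.1). 53 evaluable and 60 enrolled patients per arm, difference 0.44, SD 0.80, two-sided α 0.05, power 80% (section 2.1.2).

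**Assumed inputs, not in the document.** Correlation ρ between baseline and follow-up, 0.3 to 0.8. A within-arm shift of 0.4 SD for the power comparison. Normal data for the paired simulation and log-normal data for the four-arm simulation.

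**Step 1: the plan's own figure.** The standardised difference is 0.44/0.80 = 0.55. The two-sample t-test then needs 52.87 patients per arm, rounded up to 53, with power 0.801 at 53. The stated figure reproduces and is not in dispute; 53 is used below as the number per arm.

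**Step 2: size of the rank sum test on paired data.** An unpaired test takes the variance of the difference between two means as 2σ²/n. With pairing it is 2σ²(1 − ρ)/n. The unpaired test therefore divides by a standard error that is too large by the factor 1/√(1 − ρ), and its true size is approximately

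2 × [1 − Φ(1.96/√(1 − ρ))].

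- ρ = 0.3: 1.96/√0.7 = 2.34, size about 1.9%
- ρ = 0.5: 1.96/√0.5 = 2.77, size about 0.56%
- ρ = 0.7: 1.96/√0.3 = 3.58, size about 0.03%
- ρ = 0.8: 1.96/√0.2 = 4.38, size about 0.001%

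A simulation of the rank tests themselves (n = 53, 3,000 runs per setting) agrees:

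| ρ | Rank sum, size | Signed-rank, size | Rank sum, power at 0.4 SD | Signed-rank, power at 0.4 SD |
|---|---|---|---|---|
| 0.3 | 1.6% | 4.9% | 52% | 65% |
| 0.5 | 0.5% | 5.5% | 54% | 81% |
| 0.7 | 0.1% | 4.8% | 53% | 95% |
| 0.8 | 0 of 3,000 runs | 5.3% | 54% | 99% |

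At n = 60 and a smaller assumed shift of 0.3 SD, with ρ of 0.5, 0.6 and 0.7, the size was 0.6%, 0.45% and 0.08%. Power was 34%, 31% and 30% for the rank sum test, against 64%, 75% and 85% for the signed-rank test.

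**Step 3: the four-arm overall test.** The rank sum test is not defined for four groups, so there is no size to compute for the rule as written. One way an analyst might fill the gap is to run unadjusted pairwise rank sum tests and call the overall result significant if any is below 0.05. With four arms of 53 and no true difference (3,000 runs):

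- three comparisons with placebo: 12.9% chance of at least one false positive
- all six pairs: 19.9%
- one Kruskal-Wallis test: 4.5%

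For orientation, independent tests would give 1 − 0.95³ = 14.3% and 1 − 0.95⁶ = 26.5%. The simulated figures are lower because the pairs share arms.

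**The case against.** The strongest reply is that this is a naming slip in a condensed article and that the randomised comparison survives it. Much of that stands. ANOVA of change scores between arms is valid. A rank sum test on change scores is legitimate for any two arms, and the plan already adjusts its pairwise tests for multiplicity. The primary outcome is compared by ANOVA and is untouched. The paired-data error is conservative, so it creates no false positives, and within-arm tests are not the randomised evidence. The 13% to 20% figure depends on an unadjusted screen that the plan does not prescribe. The word ANOVA could also cover a repeated-measures form. What the reply does not remove is that the rank sum test is named, in so many words, for within-group comparison and as the test that precedes the pairwise step. That is a stated rule which has to be corrected, not a detail left to a fuller plan.

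A reader might also infer that ANOVA or the rank sum test is prescribed for the event outcomes in section 2.4.1: "the frequency of hypoglycemic events and drug-related side effects", "the incidence of acute and chronic diabetes complications" and "diabetes-related hospital admissions and emergency visit rate". In support, the chi-square test is named only for baseline: "Baseline descriptive data between the control group and the intervention groups will be compared using the chi-square test for categorical variables". But the testing sentence concerns changes in secondary variables, and these outcomes are not described as changes from baseline. The more natural reading is that the article names no test for them, which a full plan may supply. Nor would the p-values suffer much. In simulation with four arms of 60 and no true difference, ANOVA, Kruskal-Wallis and chi-square had nearly the same size on incidences (about 3% each at an assumed 2% incidence, about 6% each at 30%). ANOVA and Kruskal-Wallis stayed at 4.2% to 4.9% on over-dispersed counts.

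**Conclusion.** The rule is wrong as written, but within narrow limits: within-arm tests of change, and the overall between-arm test for non-normal continuous secondary outcomes.

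The within-arm consequence is lost sensitivity. The rank sum test works at roughly 1.6% down to below 0.1% where 5% is intended, and finds a 0.4 SD shift about 53% of the time where the signed-rank test would find it 65% to 99% of the time. The range comes from the assumed correlation of 0.3 to 0.8; the shift is also assumed. The higher the correlation, the larger the loss.

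The between-arm consequence is an undefined step. It inflates error only if it is filled badly.

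The documents do not support saying that all secondary p-values would be wrong, or that every secondary outcome is measured at all five time points.

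**What to change.** Replace the single sentence in section 2.5 with two rules.

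- **Within arms:** paired t or signed-rank test for a single follow-up visit; repeated-measures ANOVA or Friedman test over several visits, using only the visits at which Table 1 schedules that outcome. Report these results as descriptive.
- **Between arms:** for change scores that are clearly non-normal, Kruskal-Wallis as the overall test, followed by the multiplicity-adjusted pairwise comparisons already planned, done with the rank sum test. Keep ANOVA of change scores for the others.

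This is a change of wording with modest programming. Sample size, visits and data collection stay as they are. Mixed models for repeated measures or negative binomial regression would be reasonable choices, but this point does not require them.

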In animal experiments, it has been shown that compared with BBR alone, BBR combined with prebiotics has been shown to continuously reduce FBG, improve glucose tolerance, and ameliorate the balance of α- and β-cells in diabetic db/db mice (25). Similarly, Cao et al. found that the combination of BBR and prebiotics in the intervention of KKAy mice was more effective than BBR alone in blood sugar control, improvement of insulin resistance and pancreatic β-cell function, reduction of inflammatory mediators, and maintenance of intestinal barrier integrity (26). These findings suggest that the combination of BBR and prebiotics may be a novel pharmaceutical strategy for diabetes. Hence, the present study aims to evaluate the effectiveness of combining BBR and inulin on diabetes care, particularly glycemic control in patients with LADA. We will also evaluate the safety and tolerability of the combined drugs.

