Undeniably, this study has several limitations. First, the trial will be conducted only in the LADA population in China. Therefore, the results may not be directly applied to people of other races and need to be further validated by other regional or international multicenter studies in the future. Second, due to the difficulties in recruiting LADA patients, it is also not easy to maintain the balance between groups, and some participants are LADA patients who have already started drug treatment, so the results of this study may not be applicable to new-onset and mild LADA patients. In addition, the study will last for approximately one year, and the specific time of insulin use in LADA patients should be judged based on the clinical experience of the clinicians. Finally, the long-term effect of the study drugs on the gut microbial condition and complication risk of the patients is also unclear.

In conclusion, the present study will provide clinical evidence to prove the treatment effectiveness and safety of supplementation with BBR plus inulin in LADA patients. In addition, if combination medication is shown to improve blood glucose management and patient quality of life, insights gained from this study will provide new clues for future pharmacological research and clinical practices in diabetes care and glycemic control.

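### The stated rule for secondary outcomes, read as covering harms, adjusts away much of the power to show an excess on BBR plus inulin and cannot support a claim to prove safety

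*Protocol article*

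**What the plan says.** Section 2.4.1 lists as its first secondary outcome "the frequency of hypoglycemic events and drug-related side effects". Section 2.5 sets the general level, "P<0.05 was regarded as statistically significant unless otherwise specified", and then the rule for secondary outcomes: "ANOVA or Wilcoxon rank sum test will be used to compare the changes in secondary variables within and between groups". The next sentence adds: "If the difference is significant, pairwise comparisons will be performed with adjustment for multiple comparisons". Harms are not exempted. The section also provides, without any significance condition, for "frequency and percentage for categorical variables".

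On the purpose, the Introduction says "We will also evaluate the safety and tolerability of the combined drugs". The closing paragraph of the Discussion goes further: "the present study will provide clinical evidence to prove the treatment effectiveness and safety of supplementation with BBR plus inulin in LADA patients".

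**The concern.** Requiring a significant overall test and then adjusting for multiplicity protects against false claims of benefit. For harms the costly error is the opposite one, overlooking a real excess, and both devices make that error more likely. If the rule covers hypoglycaemia and side effects, the contrast that matters most for the combination, against placebo, is tested only after a significant result and then at a stricter level.

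The Discussion nevertheless promises proof of safety. Superiority tests of this kind cannot provide it. A non-significant result in arms of 53 to 60 patients is compatible with a sizeable excess, and section 2.5 states no other inferential basis for a conclusion about harms.

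**Working it through.** **Inputs from the protocol article.** Four arms, 1:1:1:1 (section 2.1). HbA1c difference 0.44%, SD 0.80%, two-sided α 0.05, 80% power, 53 evaluable and 60 enrolled per arm (section 2.1.2). P<0.05, with adjusted pairwise comparisons after significance (section 2.5).

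**Assumed.** Event proportions, because the article gives none; Bonferroni over six pairs, because no adjustment method is named; and a four-arm ANOVA on event yes/no as the overall test.

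**1. The plan's own figure.** n = 2(1.96 + 0.842)² × 0.80² / 0.44² = 51.9 per arm by the normal formula and 52.9 by the t-test version. So 53 reproduces. It was derived for HbA1c only; nothing was sized for harms.

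**2. Combination versus placebo, unadjusted, 10% versus 20%, n = 53.**
- Standard error under no difference: √(2 × 0.15 × 0.85 / 53) = 0.0694.
- Standard error under the alternative: √((0.10 × 0.90 + 0.20 × 0.80) / 53) = 0.0687.
- Power: Φ((0.10 − 1.96 × 0.0694) / 0.0687) = Φ(−0.52) = 30%.

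**3. The same with Bonferroni over six pairs.** The level is 0.05/6 = 0.0083, with critical value 2.638. Power: Φ((0.10 − 2.638 × 0.0694) / 0.0687) = Φ(−1.21) = 11%.

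**4. The full two-step procedure, by simulation at 53 per arm.** The lower figure in each range uses a two-sample z-test and the higher one the pooled four-arm error.

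| Assumed rates | Overall test significant | Overall test, then adjusted combination vs placebo | Direct, unadjusted |
|---|---|---|---|
| 10% in three arms, 20% combination | 32% | 11–15% | 30–36% |
| 10% in three arms, 25% combination | 59% | 27–36% | 54–61% |
| 20% in three arms, 35% combination | 42% | 18–22% | 42–45% |
| 10% in both non-BBR arms, 20% in both BBR arms | 37% | 11% | about 30% |

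With three pairs instead of six, the first row gives about 15% by the z-test, still half of the unadjusted 30%.

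**5. Where the loss arises.** In the first row the overall test is significant about as often (32%) as the direct comparison (30–36%). With the adjustment in place, the significance condition takes almost nothing more: with pooled error, Bonferroni alone gives 15.6% and the condition plus Bonferroni 15.4%. The fall from 30–36% to 11–15% is therefore the adjustment. The 64–70% of trials in which even the direct comparison fails reflect the sample size, and no analysis rule recovers them.

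**6. What a null result would leave open.** With 10% observed in both arms, the 95% half-width for the risk difference at 53 per arm is 1.96 × √(2 × 0.10 × 0.90 / 53) = 11 percentage points. With no events among 53 patients, the upper two-sided 95% limit is 1 − 0.025^(1/53) = 6.7%.

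**The case against.** Several objections have force.

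- **The overall test is not what hides harms.** This stands. It would be tempting to say that the overall test misses a doubling from 10% to 20% in 68% of trials and to blame the two-step structure. A direct comparison misses it about as often, so that figure describes the sample size.
- **Event rates would still be visible.** This stands. Frequencies and percentages are reported whatever the P value. They carry no between-arm uncertainty, however, so they do not support a claim of proof either.
- **The application to event counts is partly inferred.** This stands in part. The rule speaks of changes, which suits event counts poorly; the Wilcoxon rank sum test compares two groups; and chi-square is named only for baseline data. Yet harms are listed as a secondary outcome, and a step that moves on to pairwise comparisons presupposes an overall test. If the rule was not meant for harms, one sentence saying so would settle it.
- **Nobody says that non-significance means safe.** This is correct. A reader might infer from the Discussion that a non-significant result will be read as safety, but no sentence says so. *Prove* stands once, in a closing paragraph, while the Introduction's aim is to evaluate.
- **Detailed safety analysis may sit in the full protocol or SAP.** This is correct for margins, expected precision and pooled contrasts across arms, and their absence is not criticised here. The point concerns a rule that is stated and a conclusion that is stated.

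**Conclusion.** The point holds in a limited form and is worth correcting. The only inferential rule stated for secondary variables, read as covering harms, cuts the chance of showing a doubled event rate on the combination against placebo from about 30–36% to about 11–15% (53 per arm, 10% versus 20%, Bonferroni over six pairs). The multiplicity adjustment causes that loss. The significance condition adds almost nothing to it, and the low power that remains is a matter of sample size. The rule cannot support a statement that the trial will prove safety.

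The sizes rest on assumed event rates and an assumed adjustment method, and another method or number of pairs would change them. The direction does not depend on these assumptions, since any multiplicity adjustment lowers the chance of showing a real harm. The documents do not show that harms would go unreported or that a non-significant result would be declared safe.

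**What to change.** In section 2.5, exempt hypoglycaemic events, drug-related side effects and the laboratory safety measures of Table 1 from both the significance condition and the multiplicity adjustment. Both should go: an unadjusted comparison kept behind the condition would still have to pass two tests. For each active arm against placebo, whatever the overall P value, report the risk difference (or the rate ratio for hypoglycaemic episodes) with its 95% CI. In the closing paragraph of the Discussion, replace *prove* with *evaluate* for safety, in line with the Introduction.

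This takes a few sentences and no new patients or data. The price is more chance signals: nominally 5% for each contrast, and about 14% for at least one of three if they were independent (1 − 0.95³ = 0.143). The change will not make the trial well powered for harms; it reports the uncertainty openly and stops adding to it.
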